## 8.3.2 Study Populations

Male population between ages 21-49, resident in the center and outskirts of the Rwanda Military Hospital.

**Arm 1:** At least thirty three (33) adult men scheduled to undergo voluntary medical male circumcision (VMMC).

**Arm 2:** At least thirty three (33) adult men scheduled to undergo voluntary medical male circumcision (VMMC).

**Arm 3:** At least thirty three (33) adult men scheduled to undergo voluntary medical male circumcision (VMMC).

All scheduled for voluntary circumcision.

**8.3.2.1 Intent-to-Treat Population**

The intent-to-treat (ITT) population will include all patients enrolled in arms 1,2 or 3 of the study. This population will include all subjects from visit 1 that were placed with the device.

**8.3.2.2 Per-Protocol Population**

All subjects who complete the study without major protocol violations will be included in the per-protocol subset.

## 8.3.3 Primary Endpoint Analysis

Baseline demographics and patient characteristics will be presented in tabular format. The statistical evaluation of baseline characteristics will include all available data from the ITT population.

The analysis of odor levels will include database which will analyze the correlation between odor levels, subjects and subjects' partners questionnaire results.

The primary end-point evaluations will be performed based on both the ITT and the per-protocol populations.

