**Independent Blinded Reviewers (herein: Smellers):**

3 smellers will be chosen to participate in the study to perform a smell test using smell detector device; the "Nasal ranger" device, see the following link for technical information:

[http://www.nasalranger.com/Operations/Nasal%20Ranger%20Operations%20Manual%20v6.2.pdf](http://www.nasalranger.com/Operations/Nasal Ranger Operations Manual v6.2.pdf)

The Smellers will go through a short training in order to know how to operate the device and to assess their skills.

On day 0 pre procedure, the smellers will use the Nasal Ranger device to smell each of the 100 subject's genitals (baseline). Below are the room and procedure requirements. Only after the smelling procedure, will the subject undergo PrePex procedure.

The subjects will arrive to the clinic on days 3, 5 and 7 in order to document their odor levels.

On the Removal day (Day 7), the smellers will attend the Removal procedures and use the Nasal Ranger device. Below are the room and procedure requirements:

- 2 rooms will be used during the study which will have the same constant conditions (same room with no initial smell, same window, same distance from the penis: 30 cm)
- Usage of Nasal ranger device by trained personnel only
- The subjects will be randomized for their turn to enter the room
- When the smeller enters the room, the subject face will be covered and he will not wear his clothes but hospital garment
- After all 100 subjects were smelled by all 3 smellers, the subjects will be randomized again for their turn to enter the room (new randomization)
- When the smeller enters the room, the subject face will be covered and he will not wear his clothes but hospital garment
- The room should be aired between subjects
- The smelling will be always in the same distance from the genitals, by measuring with a ruler, 30 cm distance between the genitals and the end of the "Nasal Ranger"
- Each Smeller will be asked separately to grade the smell as he performs it as it is shown in the "Nasal ranger"
- Only at the end of the smelling procedure will the foreskin and device be removed.

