***Statistical Analysis:***

All data will be presented via descriptive statistics. Binary data such as adverse events success/fail criteria will be presented as a count and percentage together with an exact 95% confidence interval. Adverse event rates will be compared descriptively with the reported rates of similar treatments. Continuous data will be represented by a mean, standard deviation, median, minimum and maximum together with 95% confidence intervals for the means.

Study Flow

Screen 120 candidates

100 enrolled subjects

Randomization

Arm 1 -33 subjects

- Standard PrePex
- General hygiene instructions
- Foreskin hygiene general instructions – daily shower

Arm 2 -33 subjects

- Standard PrePex
- General hygiene instructions
- Foreskin specific hygiene instructions – daily soapy water with syringe
- **Follow up visits days 3, 5 & 7**
- Subject questionnaires
- Odor tests by 3 Blinded smellers
- Partner questionnaire – on days 3, 5 & 7
- Removal on day 7
- A random sample of subjects were evaluated a second time on day 7
- Safety - AEs

Arm 3 – 33 subjects

- Standard PrePex
- General hygiene instructions
- Foreskin specific hygiene instructions - daily chlorhexidine with syringe

|  | **Randomization & Screening Visit** | **Applying Visit** |  |  | **Removal Visit** |
| --- | --- | --- | --- | --- | --- |
| **Visit #** | **1** | **2** | **3** | **4** | **5** |
| **Day (D)/week (w)** | **–7 to D0** | **D0** | **D3** | **D5** | **D7** |
| Informed consent | X |  |  |  |  |
| Randomization | X |  |  |  |  |
| Inclusion/exclusion criteria | X |  |  |  |  |
| Medical history & Demography | X |  |  |  |  |
| Current medication including pain killers | X | X |  |  | X |
| Genital examination and potential pictures | X | X | X | X | X |
| Device apply |  | X |  |  |  |
| Foreskin Removal |  |  |  |  | X |
| Device Removal |  |  |  |  | X |
| Subject's subjective pain, tingling and discomfort evaluation |  | X | X | X | X |
| Expected Side effects and AE |  | X | X | X | X |
| Smellers test |  | X | X | X | X |
| Questionnaires for patients & for sub group female partners (between days 5-6) |  |  | X | X | X |
| Statistical analysis of data |  |  |  |  |  |

Table of Contents

[Study Synopsis 2](#__RefHeading___Toc344626056)

[Schedule of Events 8](#__RefHeading___Toc344626057)

[1. Clinical background 12](#__RefHeading___Toc344626058)

[2. STUDY OBJECTIVES AND PURPOSE 15](#__RefHeading___Toc344626059)

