# 2. STUDY OBJECTIVES AND PURPOSE

**Primary Objectives:**

- To compare the different odor levels when examine 3 arms of patients undergoing PrePex circumcision with same personal hygiene and with different foreskin hygiene techniques.

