3. STUDY ENDPOINTS

**Endpoints:**

**Primary Endpoint:**

- The primary endpoint is to assess the different odor levels by evaluating 3 arms of patients with different foreskin hygiene techniques.

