## 8.3 Statistical analysis

**Sample size:**

The intention is to obtain at least 100 evaluable subjects under Rwanda ethical responsibility (RNEC), determining to use the most deducted calculation setting and to maintain allocation ratio of 1:1:1 between the 3 study arms (33 per arm).

A sample size for the study was determined based on the two-sample t-test. In order to detect an effect size of 0.7 (Cohen's D) with 80% and at and a 5% level of significance between any two groups a sample size of 33 subjects is required. In the study each subject will have a smell test repeated by three different smellers this will be in order to examine the variability in odor sensation between different clinicians. Given this design and the three groups that will be compared, a statistically more powerful model (repeated measures ANOVA) is used instead of a t-test, and thus the study will be appropriately powered.

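### The Primary Endpoint Analysis section lists only a questionnaire correlation, and the primary endpoint fixes no day or reading round for the arm comparison

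*Protocol*

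**What the plan says.** Section 2 gives the primary objective as "To compare the different odor levels when examine 3 arms of patients undergoing PrePex circumcision" with different foreskin hygiene techniques. Section 3 gives the primary endpoint as: "The primary endpoint is to assess the different odor levels by evaluating 3 arms of patients with different foreskin hygiene techniques". It states no day, reading round or use of baseline.

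Section 8.3.3 contains baseline tables, the analysis sets and one analysis of odor: "The analysis of odor levels will include database which will analyze the correlation between odor levels" and the results of the subject and partner questionnaires. It contains no comparison of arms.

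The three-arm model is in the sample-size text of section 8.3, repeated from the synopsis: "Given this design and the three groups that will be compared, a statistically more powerful model (repeated measures ANOVA) is used instead of a t-test". The repetition described there is over assessors: "each subject will have a smell test repeated by three different smellers". Visit days are not mentioned.

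Odor is read before the procedure on day 0 (called baseline) and again on days 3, 5 and 7, according to the synopsis text on the smellers and the schedule table. On the second reading round, the synopsis says two things:
- Smellers' procedure: "After all 100 subjects were smelled by all 3 smellers, the subjects will be randomized again for their turn" to enter the room.
- Study Flow: "A random sample of subjects were evaluated a second time on day 7".

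Day 7 before removal is the time point of the study hypothesis in the synopsis introduction and the clinical background. It is not carried into the endpoint.

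**The concern.** The section that should govern the primary analysis names an analysis that does not involve the arms. An analyst working from it would report how odor readings relate to questionnaire scores, which is a different question from the primary objective.

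The endpoint leaves open which of several readings counts. If the day is chosen after the data are seen, the 5% level in section 8.3.1 no longer holds. If the days are averaged instead, power depends on when the effect appears, and no one has decided that this is wanted. If the second round is done in a sample only and its readings are pooled, some subjects contribute twice as many day-7 readings as others.

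**Working it through.** **Inputs from the protocol.** 33 per arm, d = 0.7, 80% power, 5% level (section 8.3); two-sided tests (section 8.3.1); odor on days 0, 3, 5 and 7. **Assumed:** the correlation r between days within a subject and the pattern of the effect over days. The protocol gives neither.

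**1. The stated sample size.** A two-sample t-test with d = 0.7, two-sided 5% and 80% power needs 33.02 per arm. At 33 per arm the power is 79.97%. The stated 33 is reproduced and is not in dispute.

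**2. False positives from an open choice of day.** With three independent tests, 1 − 0.95³ = 14.3%. Readings on the same man are correlated, so the risk was simulated under no arm difference: 20,000 runs, 3 × 33 subjects, one reading per subject per day, one overall F test per day on days 3, 5 and 7, and success if any p < 0.05.

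| Between-day correlation (assumed) | Risk of at least one false positive |
| --- | --- |
| 0.3 | 13.7% |
| 0.5 | 12.5% |
| 0.7 | 11.4% |
| 0.9 | 8.8% |

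The day choice alone therefore gives about 9% to 14% instead of 5%.

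**3. Averaging over days.** With T days averaged, unit variance per day and common correlation r, the effect becomes d = (mean of the daily effects) / √((1 + (T − 1)r)/T). At r = 0.5 the divisor is √(2.5/4) = 0.791 for four days and √(2/3) = 0.816 for three. Power is for one pair of arms, 33 per arm, two-sided 5%.

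| Days averaged | Daily effects (assumed) | d | Power |
| --- | --- | --- | --- |
| 0, 3, 5, 7 | 0, 0, 0, 0.7 | 0.175/0.791 = 0.22 | 14% |
| 0, 3, 5, 7 | 0, 0.3, 0.5, 0.7 | 0.375/0.791 = 0.47 | 48% |
| 0, 3, 5, 7 | 0, 0.7, 0.7, 0.7 | 0.525/0.791 = 0.66 | 76% |
| 3, 5, 7 | 0.7, 0.7, 0.7 | 0.7/0.816 = 0.86 | 93% |

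Averaging can lower or raise power relative to the planned 80%. The protocol does not say which situation applies.

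**4. Power once one day is fixed.** One pairwise contrast at d = 0.7 keeps about 80%. The overall three-arm F test with 99 subjects has 83% power if one arm differs from the other two by 0.7, and 71% if the means are 0, 0.35 and 0.7.

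**The case against.** The strongest reply is that section 8.3.3 should be read with its parent section. Section 8.3 says the three groups will be compared and names the model; section 8.3.1 gives the ITT set as primary, two-sided tests and the 5% level. Section 8.3.3 says the odor analysis will include the correlation, which does not exclude an arm comparison. This stands. A reader might infer that the protocol plans no test of its primary objective, and the documents do not support that. What remains is that the model appears only as an argument about power, is absent from the section meant to prescribe it, and has no day attached in either place.

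Two stronger figures are also tempting:
- **A false-positive risk of 20% to 30%.** This comes from nine unadjusted tests, three days by three pairs of arms. Three unadjusted pairs on a single fixed day already give about 12%, so that range mixes pairwise multiplicity with the choice of day. The share due to the day is the 9% to 14% above.
- **A fall in power to 14%.** This needs day 0 in the average and no effect on days 3 and 5. The protocol prescribes no averaging over days, calls day 0 baseline, and has cleaning done daily. It is the low end of a wide range.

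Finally, a statistical analysis plan may exist. The model terms, the summary over smellers and the use of baseline can reasonably be left to it. The time point of the primary endpoint belongs in the protocol, and a contradiction about who is read twice is not a detail that a later plan merely fills in.

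**Conclusion.** The point holds in a limited form. The only analysis named in section 8.3.3 does not address the primary objective, and the three-arm model stands only in the sample-size text. The primary endpoint fixes no day or reading round, and the synopsis gives two incompatible accounts of the second round.

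The open day raises the false-positive risk to about 9% to 14%, assuming one overall test on each of days 3, 5 and 7, any p below 0.05 accepted, and between-day correlations of 0.9 to 0.3. Averaging over days instead gives power anywhere from about 14% to 93% under the assumed patterns at correlation 0.5. These figures show what the wording leaves open; they do not predict what the sponsor would do. The stated sample size is correct for its stated inputs.

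**What to change.** In sections 3 and 8.3.3 of the protocol:
- Name the Nasal Ranger reading on day 7 before removal, first round, as the primary endpoint, in line with the protocol's own rationale.
- Move the three-arm comparison of the three smellers' readings from the sample-size text into section 8.3.3 as the primary ITT analysis, with one overall three-arm test at two-sided 5% before any pairwise comparison.
- Make days 3 and 5 and the questionnaire correlation secondary.
- State how subjects without a day-7 reading enter the ITT analysis. The PrePex procedure text allows removal on day 5 or 6, so some enrolled subjects may have none.

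In the synopsis, reconcile the smellers' procedure with the Study Flow on whether the second round covers everyone or a random sample, and state that its readings serve repeatability only.

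The cost is protocol wording. The number of subjects and the visits stay as they are. If the second round is settled as a random sample, the day-7 workload also falls.

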# ADVERSE EVENTS

## 9.1 Definitions Used in This Study to Determine Severity of Adverse Event (AE)

- Mild – Event that is noticeable but transient, requires no treatment, and does not interfere with the subject’s daily activities.
- Moderate – Sign or symptom which may be ameliorated by simple therapeutic measures: may interfere with usual activity.
- Severe - Sign or symptom that is intense or debilitating and that interferes with usual activities. Recovery is usually aided by therapeutic measures and the discontinuation of the study device may be required.

## 9.2 Definition of Adverse Event and Their Recording

AE definition: Any unfavorable and unintended sign, symptom or disease temporally associated with the use of a medical treatment and/or procedure regardless of whether it is considered related to the medical treatment/procedure (attribution of unrelated, unlikely, possible, probable, or definite).

**In this study, all expected side effects and device related or unrelated AE will be recorded in the CRF.**

The nomenclature for AE should be recorded as in the CTCAEv3 and according to the PrePex MC Classification of Adverse Events and Device Hazards.

NOTE – There may be expected procedure side effects which are not considered as Adverse

Events and will not be included in the primary safety analysis, those include:

- - Localized Edema
  - Oozing
  - Clear exudates
  - Slough (indicators: white caramel tissue over the exposed granulating tissue, may appear on day 9)

## 9.3 Definition of Serious Adverse Event (SAE)

Any adverse event experience that results in any of the following outcomes

- Death
- A life threatening event
- Requires or prolongs inpatient hospitalization or re hospitalization
- Persistent or significant disability/incapacity
- A congenital anomaly or birth defect
- Medical or surgical intervention to avoid impairment of body function

## 9.4 Guidelines to Determine the Relationship of an AE to the Study Device

- Definite: The adverse event is clearly related to the investigational treatment.
- Probable: The adverse event is likely related to the investigational treatment.
- Possible: The adverse event may be related to the investigational treatment.
- Unlikely: The adverse event is doubtfully related to the investigation treatment.
- Unrelated: The adverse event is clearly NOT related to the investigational agent(s).

## 9.5 AE Regulatory Reporting Procedures

- Any clinical study event that is judged to be a device related AE should be recorded on the Case Report Forms (CRFs) AE pages during the course of the study, as detailed in section 9.2 above. The Principal Investigator (PI) (or designee) and/or study coordinator should ensure that this information will be captured during every study subject visit. Any information that is recorded in the CRF must rely on records in the source document. In this study working sheets are allowed as source documents.
- Whenever a study subject has reported **any** device related AE, the study coordinator or PI designee will discuss the event as soon as possible with the PI (if possible while the study subject is there). The PI must evaluate the event.
- If the AE is not serious, the information will be recorded on the appropriate CRF AE Form as instructed above. The AE will be managed medically as appropriate, and will be followed until resolution.
- Any SAE (according to the definitions above), whether or not related to the investigational product, must be reported by the PI or designee simultaneously to the sponsor’s representative, to the Ethical Committee and to the board immediately (within **24 hours** after learning of the event) for accurate and timely recording and reporting by the CRF's SAE Form and managed medically as appropriate, and will be followed until resolution. At intervals per PI discretion, a follow-up CRF SAE Form will be filled and sent to the sponsor's representative. Any relevant information available on the event (hospital records, lab tests, discharge summaries, etc.) will be applied to determine whether the SAE is Unexpected AND related to the investigational product and requires reporting the event to the Ethical Committee and to the MOH ("Expedited Safety Report", see section 9.6 ahead). Any additional information on the SAE should be also forwarded to the sponsor’s representative for further follow-up on special SAE follow-up forms.

Each SAE will be summarized in a form of a "SAE Report".

- **All SAE Reports shall be sent to the Ethics Committee periodically, unless in the following incidences:**

**- Within 48 hours of learning of event occurrence in case of any unexpected** **and device related** **SAE**.

- For reasons of confidentiality, subject identifying data (e.g., name, social security numbers) should not be disclosed outside the hospital whatsoever. Instead, the study-specific code number should be used.

Sponsor representatives will provide direction for consistent and systematic handling of such reports and determine their responsibility to the Health Authority as stipulated by applicable MDR regulations. Only **Investigational Product Related and Unexpected SAE’s** will be reported to the Health Authorities. Therefore, not all SAEs/Product Complaints reported to Sponsor will require subsequent notification to the Health Authority. However study investigators will be informed by clinical study personnel of any serious adverse event and product complaint reported to the Health Authority associated/related to the medical device used in this study.

Sponsor clinical and medical teams will review all **unexpected and related SAE’s** to evaluate them for further recommendation of study status, as well as other device related AE incidence evaluation.

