**Primary Objectives:**

- Safety - To determine the adverse events rate per foreskin cleaning technique per study arm
- Efficacy - To compare the different odor levels when examine 3 arms of patients undergoing PrePex circumcision with same personal hygiene and with different foreskin hygiene techniques

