**PrePex MC**

**Classification of Adverse Events and Device Hazards**

| **Adverse**  **Event** | **Description** | **Severity** | **Code** |
| --- | --- | --- | --- |
| **A. During Placement** | | | |
| Pain | Pain score of 8 or more not requiring anesthesia  Requires anesthesia  Not controlled by additional anesthesia | Mild  Moderate  Severe | APP1  APP2  APP3 |
| Difficulty in applying the device | Could not apply device; determined as contra indicated; no harm to tissue or subject  Had to push unusually hard, but no harm to tissue or subject and no change to procedure  The device cut through the foreskin, with or without minor bleeding, No change in procedure  The device cut through the foreskin, with or without minor bleeding, and requiring a change to surgical method  The device cut through the foreskin, causing significant bleeding and requiring a change to surgical method | No AE  No AE  Mild  Moderate  Severe | --  --  ADD1  ADD2  ADD3 |

| **Adverse**  **Event** | **Description** | **Severity** | **Code** |
| --- | --- | --- | --- |
| **B. While Wearing the Device** | | | |
| Pain / Discomfort | Not requiring intervention beyond painkiller or anesthetic cream  Requiring early device removal by PrePex Operator or by client  Requiring early device removal and anesthesia  Not controlled by device removal or additional anesthesia | Not AE  Mild  Moderate  Severe | --  BWP1  BWP2  BWP3 |
| Device displacement / spontaneous detachment | Device displacement with no clinical consequences  Complete spontaneous detachment, or patient removed device himself with no adverse clinical consequences  Device displacement requiring re-placement  Device displacement requiring surgical intervention  Displacement or detachment and penile damage present | Not AE  Mild  Moderate  Severe | --  BDD1  BDD2  BDD3 |
| Early device removal (i.e. 4 days or less with the device) | Device removed due to pain, swelling or bleeding  Device removed due to pain, swelling or bleeding requiring surgical intervention  Device removed and penile damage present | Mild  Moderate  Severe | BER1  BER2  BER3 |
| Edema | More edema than usual but not causing any discomfort to the patient  Moderate edema causing the patient discomfort, though managed with conservative measures  Severe edema, causing the patient discomfort, uncontrolled with conservative measures | Mild  Moderate  Severe | BED1  BED2  BED3 |

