| Hematoma | Mild contained hematoma, not requiring any treatment  Hematoma requiring surgical drainage/exploration but no evidence of active bleeding  Rapidly expanding hematoma suggesting active bleeding requiring surgical exploration or referral | Mild  Moderate  Severe | BHM1  BHM2  BHM3 |

| **Adverse**  **Event** | **Description** | **Severity** | **Code** |
| --- | --- | --- | --- |
| **C. During Device Removal** | | | |
| Pain | Pain score of 6 or less lasting for less than 2 minutes  Pain score of 8 or more lasting for over 2 minutes  Requires anesthesia  Not controlled by additional anesthesia | Not AE  Mild  Moderate  Severe | --  CPR1  CPR2  CPR3 |
| Excessive bleeding | More bleeding than usual, but easily controlled  Bleeding that requires suture to control  Blood transfusion or transfer to another facility for management required | Mild  Moderate  Severe | CBL1  CBL2  CBL3 |
| Edema | More edema than usual but not causing any discomfort to the patient  Moderate edema causing the patient discomfort, though managed with conservative measures  Severe edema, causing the patient discomfort, uncontrolled with conservative measures | Mild  Moderate  Severe | CED1  CED2  CED3 |
| Hematoma | Mild contained hematoma, not requiring any treatment  Hematoma requiring surgical drainage/exploration but no evidence of active bleeding  Rapidly expanding hematoma suggesting active bleeding requiring surgical exploration or referral | Mild  Moderate  Severe | CHM1  CHM2  CHM3 |
| Infection | Pain and erythema with no obvious swelling  Painful swelling with erythema or elevated temperature or purulent wound discharge  Cellulitis or wound necrosis | Mild  Moderate  Severe | CIN1  CIN2  CIN3 |
| Device removal difficulties | Difficult removal, with pain score of 8 or more lasting for over 2 minutes  Difficult removal, with abrasion of shaft or glans  Difficult removal, requiring injection of local anesthetic or requiring up to three sutures post-removal  Difficult removal, requiring more than three sutures  Difficult removal, with penile damage | Mild  Mild  Mild  Moderate  Severe | CDR1.1  CDR1.2  CDR1.3  CDR2  CDR3 |
| Damage to the penis | Mild bruising or abrasion, not requiring treatment  Bruise or abrasion to the glans or shaft of the penis requiring pressure dressing or surgery to control  Portion or all of the glans or shaft of the penis severed | Mild  Moderate  Severe | CDP1  CDP2  CDP3 |

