**Other AEs**

- Liver or pancreatic abnormalities;
- Neurologic conditions of the central nervous system (e.g., meningitis, encephalitis, convulsions and headaches, visual and auditory disturbances, strokes), and peripheral neurologic conditions (e.g., peripheral neuropathies, motor weakness etc.);
- Myocarditis and pericarditis;
- Dermatologic condition affecting the genital, pubic or perianal areas or groin; and,
- Injuries and accidents.

Common illnesses unrelated to male circumcision will not be included in the “other AE” category to avoid unnecessary reporting of irrelevant events. Such AEs include the following:

- Malaria and other common parasitic infections;
- Gastrointestinal (GI) tract diseases, including diarrhea, gastroenteritis (bacterial, viral or parasitic), and other GI conditions, and oropharangeal infections;
- Respiratory illnesses (Upper Respiratory Tract Infections, acute lower respiratory infection, pleurisy), including tuberculosis, influenza or other respiratory infections;
- Angina, myocardial infarction, congestive cardiac failure;
- Dermatologic conditions (e.g., scabies, infected and uninfected rashes, pruritis, fungal infection), except those affecting the genital, pubic or perianal areas or groin
- Neoplasms not affecting the genitourinary tract; and,
- Surgical conditions not related to the intervention (e.g., hernias) and which do not require hospitalization.

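### Section 9.5 ties AE-page recording and investigator review to device relatedness, at odds with Section 9.2; followed literally, it could understate the AE rate per cleaning technique

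*Protocol*

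**What the plan says.** **Objective.** Section 8.2 randomises men to three ways of cleaning the foreskin: washing in the daily shower, soapy water by syringe, or diluted chlorhexidine by syringe. Every arm has the standard PrePex procedure. The Study Synopsis has two lists of primary objectives. The later one, just before Statistical Considerations, includes "To determine the adverse events rate per foreskin cleaning technique per study arm". The earlier list and Section 2 do not make this primary, but both name the safety of the cleaning procedure among the secondary objectives, and Section 3 does so among the secondary endpoints.

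**Recording.** Section 9.2 defines an AE without regard to cause and says in bold that expected side effects and "device related or unrelated AE will be recorded in the CRF". Section 9.5 says "Any clinical study event that is judged to be a device related AE should be recorded on the Case Report Forms (CRFs) AE pages", adds that this follows Section 9.2, and then requires discussion with, and evaluation by, the principal investigator whenever a device related AE is reported. Section 9.5 also requires any SAE to be reported within 24 hours whatever its relation to the product.

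**Attribution.** The heading of Section 9.4 speaks of the study device. Its five grades refer to an *investigational treatment* or *investigational agent(s)*, and neither term is defined. The only product described in Section 5 is the PrePex device.

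**Counting and coding.** A note in Section 9.2 introduces localized edema, oozing, clear exudates and slough with the words "Events and will not be included in the primary safety analysis, those include". The appended PrePex classification grades edema as an AE up to "Severe edema, causing the patient discomfort, uncontrolled with conservative measures". Part B of the appendix (while wearing the device) has no infection row; parts C, D and E each have one. Genital skin conditions appear in the Other AEs list, with no severity grade and no code.

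**The concern.** Two recording rules are in force and they are not the same. The narrower one filters on the factor that all arms share (the device), while the safety question is about the factor that differs (the cleaning technique). A non-serious irritation from chlorhexidine, or a minor injury from the syringe, is the kind of event on which the arms could differ. It is also the kind that a nurse could reasonably judge not to be device related.

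The trial is open label and blinding is described only for the odor assessors, so that judgement would be made with the arm known and could itself vary by arm. An event that never reaches the CRF cannot be recovered by any later analysis. What is at stake is a per-arm AE rate that is too low, possibly by different amounts in different arms, in a study meant to support a cleaning procedure with low odor and no loss of safety.

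**Working it through.** The point rests on the text. The protocol states no figure for it, so there is none to reproduce.

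**1. The recording rules side by side**

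| Place | Events covered | Depends on device relatedness? |
| --- | --- | --- |
| 9.2, AE definition | any unfavorable event in temporal association | no |
| 9.2, bold rule | all AEs and expected side effects, into the CRF | no |
| 9.5, first bullet | events judged device related, onto the CRF AE pages | yes |
| 9.5, second bullet | device related AEs, to the principal investigator | yes |
| 9.5, SAE bullet | all SAEs, within 24 hours | no |

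Section 9.5 cites Section 9.2 as its source but states a narrower rule. Its order is also awkward: the relatedness judgement comes before the principal investigator's evaluation that it triggers.

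**2. What the filter can remove.** Write an arm's true non-serious AE risk as device-caused risk plus cleaning-caused risk. The first part is expected to be similar across arms; the second is the randomised contrast. A device-relatedness filter keeps the first and can remove the second.

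**3. Attribution.** Read by its heading, Section 9.4 has no place for a reaction to the cleaning agent. Read by its grades, such a reaction might be covered. The text does not settle which.

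**4. Part B.** Cleaning takes place while the device is worn, and the schedule of events collects AEs on days 3 and 5. An infection seen then has no row in part B. One still present at removal can be coded in part C.

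**5. Edema.** The Section 9.2 exclusion carries no threshold. The lowest appendix class is edema beyond the usual amount without discomfort. The two can be read as usual against more than usual, but the protocol does not say so.

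**6. Severity at removal.** "Difficult removal, requiring injection of local anesthetic or requiring up to three sutures post-removal" is classed Mild. In the same part C table, a suture needed to control bleeding and pain that needs anesthesia are Moderate. Section 9.1 describes Mild as "Event that is noticeable but transient, requires no treatment". For removal pain, the score-based entries leave a score of 7, or of 8 or more for under 2 minutes, without a class.

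**7. Illustration of size (assumed events and risks, 33 men per arm)**

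- One man missed: 1/33 = 3.0 percentage points.
- Two men missed: 2/33 = 6.1%, exact (Clopper-Pearson) 95% CI 0.7% to 20.2%, against a recorded 0%.
- Zero recorded: exact 95% upper limit 1 − 0.025^(1/33) = 10.6%, valid only if recording is complete.
- With a true cleaning-caused risk of 10% and a fraction s of these events recorded, P(none recorded) = (1 − 0.10 × s)^33:

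| s | Expected recorded (33 × 0.10 × s) | P(none recorded) |
| --- | --- | --- |
| 1 | 3.3 | 3.1% |
| 0.5 | 1.65 | 18.4% |
| 0.25 | 0.83 | 43.4% |
| 0 | 0 | 100% |

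At a true risk of 20% the same four rows give 0.06%, 3.1%, 18.4% and 100%.

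**The case against.** The best defence is that Section 9.5 defers to Section 9.2. It does not contain the word *only*, it concerns regulatory reporting, and its bullet on non-serious AEs sends them to the AE form without repeating the device limit. A site that reads both sections would record everything. This stands, and it limits the point to a conflict that sites can resolve differently. It does not remove the conflict, because the first two bullets of Section 9.5 still name device related AEs.

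Four stronger readings are tempting, and the documents do not support them:

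- **That reactions to the cleaning agent are bound to be hidden.** The Other AEs list names genital skin conditions, its exclusions spare them, and Section 9.2 also calls for CTCAEv3 nomenclature. Such events are recordable, though the appendix gives them no grade or code.
- **That Section 9.4 judges relation to the device alone.** Only its heading does. The fair criticism is ambiguity.
- **That serious cardiac events would be lost**, because "Angina, myocardial infarction, congestive cardiac failure" stands among the illnesses kept out of the Other AEs category. That list concerns one appendix category, and an event meeting the SAE definition in Section 9.3 is reported whatever its relation.
- **That severe edema is excluded from the safety analysis.** The exclusion is for expected side effects, and usual against more than usual is a natural reading. What is missing is the explicit threshold.

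The severity inconsistencies at removal are real but secondary. Removal is common to all arms, and the sutures and anesthesia entries change a grade, not whether an event is counted.

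**Conclusion.** The point holds as a conflict between Sections 9.5 and 9.2 that could understate the non-serious AE rate per cleaning technique. It rests on two conditions: that a site follows Section 9.5 literally, and that a reaction to the cleaning agent or syringe is judged not device related. If either fails, recording is complete. SAEs are not affected in any case.

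No size can be derived from the protocol. The 3.0 points per man missed is arithmetic on 33 men; the 6.1% example and the recording fractions are assumptions. The 0.34% device-related AE rate quoted from the nurses' cohort study is no yardstick here, since those men were followed for 8 weeks after removal and this study ends at removal.

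A correction is still worth making before enrolment, because the loss, if it occurs, falls on the randomised contrast and cannot be repaired afterwards.

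**What to change.** 1. **Section 9.5:** for both CRF recording and principal investigator review, replace the reference to device related AEs with AEs whatever their relation, to match Section 9.2.
2. **Section 9.4:** record relatedness twice, once to the device and once to the assigned cleaning procedure (agent and syringe), and define the terms used in the grades.
3. **Appendix part B:** add an entry for infection and local irritation, so that events on days 3 and 5 can be coded by arm.
4. **Section 9.2 note:** state that the edema exclusion covers only edema below the lowest class graded in the appendix.
5. **Severity:** reconcile the classes for sutures, anesthesia and removal pain in appendix part C with one another and with the Mild definition in Section 9.1, and close the gap in the pain classes. The choice of grade is for the clinical team.

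The cost is protocol wording, one extra CRF field for the second attribution, and a few more AE entries at visits already scheduled. No new visits or subjects are needed.
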